### Variables and instruments

Participants of the intervention group complete a questionnaire at baseline, at the end of the intervention as well as six months post-intervention. Participants in the control group complete the questionnaire-set at equal intervals without receiving any intervention. The questionnaire-set contains socio-demographic information, standardized instruments to measure ED risk as well as ED risk factors, a knowledge test and an additional set of evaluative questions (only within the intervention condition of the study). Participants complete each questionnaire-set in class while trained research assistants with a background in clinical psychology answer any questions. No incentives for participation or feedback about individual test results are given to the participants.

#### Socio-demographic variables

Socio-demographic variables include school year (grade), Body Mass Index (BMI, weight in kilograms divided by height in meters squared), parental educational level, participants’ current romantic relationship status, parental marital status, immigrant background as well as number of siblings, number of friends and amount of physical activity per week.

#### ED risk

ED risk is assessed by the German version of the Children’s Eating Disorder Examination-Questionnaire (Ch-EDE-Q, [39]). The Ch-EDE-Q is the children’s version of the Eating Disorder Examination Questionnaire (EDE-Q) for participants below the age of 16 years. The questionnaire assesses specific ED psychopathology on four subscales, which are restraint, eating concern, weight concern and shape concern. The calculation of subscale means as well as a total mean score is possible. The global score has a range from 0–132 points. Receiver Operating Characteristic (ROC) analysis showed an optimal trade-off between specificity and sensitivity at a mean global score of 2.3 (Se = .92, Sp = .86) with the EDE as diagnostic reference [40]. The psychometric properties of the Ch-EDE-Q have been shown to be satisfactory. It has adequate internal consistency in clinical samples (.65 ≤ Cronbach’s α ≤ .88), excellent inter-rater reliability for the subscale scores as well as the global score (.98 ≤ r_icc_ ≤ .99) and acceptable retest reliability (.24 ≤ r_tt_ ≤ .44). Convergent and discriminant validity are also satisfactory [41].

#### Knowledge about ED

A 20-item questionnaire has been developed for the purposes of this study. It comprises questions regarding the content of the three units of the prevention program. Each question can be answered with “right”; “wrong” or “don’t know”. Every correctly answered question is given one point which is then added to give a sum-score. A maximum sum score of 20 points is, therefore, possible.

#### Internalization of Western beauty ideals

The internalization of Western beauty ideals transferred by the media is measured by the German version of the Sociocultural Attitudes Towards Appearance Questionnaire (SATAQ-G, [42]). The questionnaire assesses socio-cultural influences on body image with three subscales: general internalization, awareness about media based beauty ideals as well as perceived pressure from the media to conform to beauty ideals. The questionnaire is available in gender-adapted versions, thereby taking the different body ideals of girls and boys into account. The instrument has been shown to be reliable with good internal consistency of the subscales (.75 ≤ Cronbach’s α ≤ .89) and acceptable convergent validity for the internalization and pressure subscales [43].

#### Body dissatisfaction

Figure drawings from the Kid’s Eating Disorder Survey (KEDS, [44]) are used as a measure of body dissatisfaction. Eight figure drawings with increasing weight and size of body shape are presented for both sexes. Participants are asked to highlight their own real as well as their ideal body shape. The figure drawings are numbered in ascending order, “1” indicating the thinnest, and “8” indicating the largest body. Body dissatisfaction is calculated by subtracting the ideal from the real body shape. The KEDS has been shown to be a reliable instrument and the self-reported real body shape adequately represents current BMI [45].

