**Psychosocial risk factors**	
Internalization of Western beauty ideals	[14,15,17]
Adverse life events (e.g. sexual abuse)	[2,11-13]

Children and adolescents are at particular risk of developing EDs. In AN, for example, there is evidence of two peaks of onset, one before 15–16, the other after 18 years [18]. BN and BED occur later with an average age of onset of approximately 20 years in BN and BED [10]. In addition, the beginning of subclinical levels of eating pathology and disordered eating behavior has been observed in this age range. The German Federal Center for Health Education (BZgA) has reported that more than half of German 13- to 14-year-olds would like to be thinner [19]. Another study with 14- to 18-year-olds showed that 42% of boys and 53% of girls preferred a thin body ideal, 18% of the boys and 19% of the girls were currently trying to lose weight and 17% of the children with a normal weight felt too fat [20]. Moreover, 28.9% of the 11- to 17-year-old girls and 15.2% of the boys showed pathological eating behavior [21]. Such results suggest, therefore, that school age might be an ideal time to implement preventive interventions.

The media might play an important role in the internalization of Western beauty ideals. It is estimated that only one out of every 40.000 women meets the height, weight and body shape criteria of professional models [22], which can lead to body dissatisfaction. This body dissatisfaction is often accompanied by depressive states [23,24] as well as low self-esteem [25] and makes the development of an ED more likely [15].

Schools offer a convenient framework for the implementation of preventive interventions. Children are exposed to social pressure at school which is a significant factor in the development of a negative body image as well as weight concerns in girls and boys alike [26]. Another advantage of schools as the setting for prevention interventions is the possibility to reach a large number of people at the same time. Many previous interventions have only included small samples (for an overview see [27]). Since prevention should benefit individuals as well improve collective health [28], programs should reach as many individuals as possible.

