### Secondary outcome

Knowledge about EDs, internalization of Western beauty ideals, body dissatisfaction, self-concept as well as symptoms of depression and anxiety are considered to be secondary outcomes.

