### Study hypotheses

It is hypothesized that the prevention program reduces the individual ED risk in participants of the intervention group compared to the control group. It is also expected that, participants of prevention program have increased knowledge about EDs, decreased body dissatisfaction and symptoms of depression as well as anxiety compared to the control group.

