### Statistical analyses

In order to empirically test the hypotheses regarding differences between the intervention and control groups at the 6-month follow-up, multi-level analyses are conducted with school as a random factor as well as sex (male vs. female), grade (8th vs. 11th), parents’ educational level (lower- both parents vs. higher – one parent vs. higher both parents) and group (intervention vs. control) as fixed factors and baseline ChEDE-Q scores as covariate. Two-sided tests with an alpha level of p < .05 and regression coefficients with 95% confidence intervals (CI) are calculated in all analyses. Analyses are first performed on completers and then sensitivity analyses are conducted using imputed data.

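### Body dissatisfaction is scored as a signed difference, so for pupils who want a larger body the hypothesised decrease points the wrong way and the group effect on this secondary outcome is attenuated

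*Protocol article*

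**What the plan says.** In the protocol article, the section Body dissatisfaction describes the instrument: "Eight figure drawings with increasing weight and size of body shape are presented for both sexes". On the coding it says: "The figure drawings are numbered in ascending order, “1” indicating the thinnest, and “8” indicating the largest body". Pupils mark their real and their ideal shape, and the scoring rule follows: "Body dissatisfaction is calculated by subtracting the ideal from the real body shape". The section mentions no absolute value, no recoding and no split by direction, and no other section changes the rule.

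Under Secondary outcome, body dissatisfaction is one of several secondary measures. Under Study hypotheses it is given a direction: the intervention group is expected to show "decreased body dissatisfaction and symptoms of depression as well as anxiety compared to the control group".

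Under Statistical analyses, boys and girls are analysed together. Sex, grade, parental education and group are fixed factors and school is a random factor. No interaction of sex with group is stated.

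The section on the internalization questionnaire explains that the instrument comes in versions for each sex, "thereby taking the different body ideals of girls and boys into account".

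**The concern.** A score on which a decrease means improvement needs its best value at the bottom of the scale. Here the best value, satisfaction, lies in the middle. For pupils who want to be thinner, a lower score does mean less dissatisfaction. For pupils who want to be larger, it means more.

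Two consequences follow for the group coefficient. First, a pupil in the second group who becomes satisfied pushes the mean up, which the hypothesis reads as deterioration. Second, if the programme helps both groups, their changes have opposite signs and partly cancel. The trial enrols whole classes of both sexes, not a selected group in which only the wish to be thinner need be considered. At stake is the interpretation of one of the few secondary outcomes for which the article states a direction.

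**Working it through.** The article gives no mean, variance or power figure for this outcome, so there is no stated result to reproduce. The check has four steps.

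**1. Properties of the score.** Inputs are the coding 1 to 8 and the rule real minus ideal, both from the section Body dissatisfaction.
- Range: 1 - 8 = -7 to 8 - 1 = +7.
- Of the 8 × 8 = 64 possible pairs, 28 are negative (wants larger), 8 are zero (satisfied) and 28 are positive (wants thinner).
- With the absolute difference the range is 0 to 7, and satisfied is the minimum.

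**2. One pupil.** Real 3, ideal 5:
- Signed score 3 - 5 = -2, which is below the satisfied value of 0.
- If this pupil becomes satisfied, the signed score changes by 0 - (-2) = +2 and the absolute score by 0 - 2 = -2. The same improvement carries opposite signs.
- One pupil at +2 and one at -2 have a signed mean of 0, the same as two satisfied pupils. Their absolute mean is 2.

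**3. Group means, under assumptions.** Let a share t want to be one step thinner (+1) and a share q want to be one step larger (-1), with the rest at 0. Suppose the programme halves the discrepancy in both groups, for instance by making half of each group satisfied.
- Signed mean without the programme: t - q. Effect: -(t - q)/2.
- Absolute mean without the programme: t + q. Effect: -(t + q)/2.

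With t = 0.5 (an assumption) and a range for q:

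| q | signed effect | absolute effect |
|---|---|---|
| 0 | -(0.5 - 0)/2 = -0.25 | -(0.5 + 0)/2 = -0.25 |
| 0.1 | -0.20 | -0.30 |
| 0.2 | -(0.5 - 0.2)/2 = -0.15 | -(0.5 + 0.2)/2 = -0.35 |
| 0.3 | -0.10 | -0.40 |
| 0.4 | -0.05 | -0.45 |
| 0.5 | -(0.5 - 0.5)/2 = 0.00 | -(0.5 + 0.5)/2 = -0.50 |

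At q = 0 the two scores agree. At q = 0.2 the signed effect is 0.15/0.35, or about 43%, of the absolute one. It vanishes when q equals t, and its sign reverses only when q exceeds t. More generally, if shares a and b of the two groups become satisfied, the signed change is -at + bq. Reversal then needs bq to exceed at.

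**4. Whether the model repairs this.** A fixed factor for sex lets boys and girls have different mean levels. It leaves one common group coefficient, which still averages over pupils for whom improvement has opposite signs, and it does nothing about both directions occurring within one sex. The two-sided test does not help, because the difficulty lies in what the coefficient means.

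**The case against.** The strongest reply is that real minus ideal is a legitimate measure of the wish to be thinner, which is the more obvious concern in an eating-disorder trial. The Background leans that way: it reports that more than half of German 13- to 14-year-olds would like to be thinner and that 17% of normal-weight children felt too fat. An absolute score gives a wish to be larger the same weight as a wish to be thinner, which has an interpretive cost of its own. This stands as an argument about the construct. It does not rescue the text, because the article calls the score body dissatisfaction and does not restrict it to the thinner direction.

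A second reply is that the article is condensed and an analysis plan may hold more detail. That would excuse silence. Here, however, the article does state a scoring rule, and the rule as stated conflicts with the direction of the hypothesis.

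Three stronger readings are tempting and are not supported.
- The Background reports that "42% of boys and 53% of girls preferred a thin body ideal". A reader might take the complements, 58% of boys and 47% of girls, as pupils who want a larger body. They are not. They include satisfied pupils, who score 0, and heavier pupils with a non-thin ideal, who can score above 0. The figure does not show how many want to be larger.
- A reader might infer a null or wrong-signed result as the expected outcome. A symmetric example, such as 40% at +1, 40% at -1 and 20% at 0, does leave the signed mean at 0 while the absolute mean falls from 0.8 to 0.4. But equal shares build the full cancellation in. When fewer pupils want to be larger than thinner, and the programme works equally on both, the result is attenuation.
- A reader might treat this as a threat to the trial's main conclusion. The primary outcome is the Ch-EDE-Q global mean score, and the sample size does not rest on the figure drawings.

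**Conclusion.** The point holds in a limited form. As written, the score and the hypothesis point the same way only for pupils who want to be thinner. For those who want to be larger, improvement is recorded as harm. This follows from the scoring rule and needs no assumption.

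The size does need assumptions. With half of pupils wanting to be one step thinner and all discrepancies halved, a 20% share wanting to be larger reduces the visible effect to -0.15, against -0.35 on the absolute score. The effect could be null or reversed if the wish to be larger were as common as the wish to be thinner or more so, or if the programme acted mainly on it. The article gives no share from which to judge this. The best support in the text for expecting both directions is its acknowledgement that the body ideals of girls and boys differ, and that carries no number.

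This should be fixed, as a matter confined to one secondary outcome.

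**What to change.** Define body dissatisfaction for the group comparison as the absolute value of real minus ideal, so that 0 is the best score and a decrease always means less dissatisfaction. As a supplement, report by sex either the signed score or the wish to be thinner and the wish to be larger separately. Fix this before the outcome is analysed.

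The cost is small: both ratings are already collected, so no new data are needed and one line of scoring code changes. The drawbacks are that the absolute score is bounded at zero, is more skewed, and weights both directions equally. The supplementary results by direction and sex let a reader recover the information lost through that equal weighting.

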#### Self-concept

Self-concept is assessed with the German version of the Multidimensional Self Concept Scale (MSWS, [46,47]). This instrument measures self-concept on six different subscales: emotional self-concept, security in social situations, handling criticism, performance-related self-concept, physical attractiveness and athletic self-concept. Psychometric qualities of the instrument are satisfactory with an internal consistency of α = .93 and well demonstrated convergent, discriminant and construct validity [47].

#### Symptoms of depression

Symptoms of depression are assessed with the depression module of the Patient Health Questionnaire (PHQ-9, [48,49]). The self-assessment scale consists of nine items and it is able to establish provisional depressive disorder diagnoses and grade depressive symptom severity [50]. The questionnaire is reliable with an internal consistency of α = .89 and a retest-reliability of r_tt_ = .84 [51].

#### Anxiety

Anxiety is assessed by the 7-item Generalized Anxiety Disorder Scale (GAD-7, [52]). There is evidence that the GAD-7 has good reliability as well as criterion, construct, factorial and procedural validity [53].

### Sample size/power calculation

Participants are adolescents of grades 8 and 11 (age 14 and 17 years). Based on previous studies [46] an effect size of Cohen’s d = 0.3 is expected. For a two-sided test with a type-I error rate of 5% and power of 80%, two samples with 176 participants each (N = 352) are needed to reach statistical significance. Given that cluster effects, expected inter-class correlations of 0.05 as well as an average cluster size of 65 participants need to be considered, the design factor is 4.2. Thereby at least 1478 participants need to be recruited. If an additional drop-out-rate of 25% is assumed then a total of 1848 participants are needed to be recruited.

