**Methods/Design:**

The gender-adapted prevention program extends over six school hours. It contains interactive and educational elements about eating disorders and their treatment. Participants pass through different exercises and reflect on the influences of the media, self-esteem, body perception and individual resources. A cluster-randomized controlled trial is chosen to evaluate the program. Based on an estimated effect size of d = 0.3 a total of 1848 participants are enrolled in the study. Eating disorder risk, internalization of Western beauty ideals, body dissatisfaction, self-concept as well as anxiety and symptoms of depression are measured before and immediately after the intervention as well as at a six-month follow-up. In addition, the intervention group evaluates the different components of the program.

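### The 25% drop-out allowance is multiplied on instead of divided out, so 1848 recruits leave 1386, below the plan's own minimum of 1478

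*Protocol article*

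**What the plan says.** The section Sample size/power calculation of the protocol article builds the total in four steps.

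1. Effect size: "an effect size of Cohen’s d = 0.3 is expected". The test is two-sided at 5% with 80% power.
2. Unclustered size: "two samples with 176 participants each (N = 352) are needed to reach statistical significance".
3. Clustering: "expected inter-class correlations of 0.05 as well as an average cluster size of 65 participants need to be considered", from which "the design factor is 4.2". The result is "Thereby at least 1478 participants need to be recruited".
4. Drop-out: "If an additional drop-out-rate of 25% is assumed then a total of 1848 participants are needed to be recruited".

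The abstract (Methods/Design) repeats the total, "a total of 1848 participants are enrolled in the study", with the effect size but without a drop-out rate or a power.

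Three other sections bear on the point. Primary outcome places the endpoint six months after the programme. Statistical analyses puts completers first, uses imputed data only for sensitivity analyses, and includes the baseline Ch-EDE-Q score as a covariate. Study registration gives a trial title that names 20 schools and records that recruitment has ended.

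**The concern.** The figure of 1478 comes before any drop-out allowance and derives from the number needed for the test. It is therefore the number that must still have data at six months. A drop-out rate is a proportion of those who enter. Adding 25% of 1478 on top of 1478 does not restore 1478 once a quarter of the larger total is lost.

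The first analysis is on completers, so pupils without six-month data do not count towards it. The section Methods to reduce bias also treats surveys judged to be misrepresented as drop-outs. At stake is whether the headline total does what the section implies, namely keep the required number in the analysis at the loss the plan itself assumes.

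**Working it through.** **Inputs** (Sample size/power calculation unless noted): d = 0.3; two-sided α = 5%; power 80%; 176 per arm; intracluster correlation 0.05; average cluster size 65; design factor 4.2; minimum 1478; drop-out 25%; total 1848. Number of schools: 20 (Study registration).

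**Reproducing the plan's figures**

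- Two-sample t-test, 176 per arm: power 80.1%. With 175 per arm it is 79.9%, so 176 and N = 352 are right.
- Design factor: 1 + (65 − 1) × 0.05 = 4.2.
- Clustered size: 352 × 4.2 = 1478.4, given as 1478.
- Drop-out as applied: 1478.4 × 1.25 = 1848.0. This matches the stated total exactly.

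**Checking the drop-out step**

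- Left after 25% drop-out: 1848 × 0.75 = 1386.
- Shortfall against the minimum: 1478 − 1386 = 92 (6.2% of 1478).
- Drop-out that 1848 does cover: 1 − 1478.4 / 1848 = 20.0%.
- Recruits needed at 25%: 1478 / 0.75 = 1970.7, so 1971. The unrounded 1478.4 / 0.75 = 1971.2 gives 1972. Either is 123 to 124 more than 1848.

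**Effect on power**

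Effective N = analysed N / design factor. Power (normal approximation) = Φ(0.3 × √(effective N / 4) − 1.96). The t-test column uses the noncentral t distribution with individual-level degrees of freedom.

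| Case | Design factor | Effective N | Power, normal | Power, t-test |
|---|---|---|---|---|
| 1478.4 analysed, 65 per school | 4.2 | 352 | 80.4% | 80.1% |
| 1386 analysed, 65 = analysed size | 4.2 | 330 | 77.8% | 77.5% |
| 1386 analysed in 20 schools (69.3 each) | 4.415 | 314 | 75.7% | 75.5% |
| 1386 analysed, 65 = recruited size (48.75 analysed) | 3.39 | 409 | 85.9% | 85.7% |

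For the second row: 1386 / 4.2 = 330, and 0.3 × √82.5 − 1.96 = 0.765, so Φ = 0.778. The design factors in the last two rows are 1 + 68.3 × 0.05 = 4.415 and 1 + 47.75 × 0.05 = 3.3875.

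**The case against.** A reader might infer that the trial will not have 80% power. The documents do not support this as a flat statement, for two reasons.

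**The meaning of 65 is not given.** If 65 is the recruited cluster size and losses fall evenly across schools, clusters shrink to 48.75, the design factor falls to 3.39 and power rises to about 86%. The article does not rule this out. It fits poorly with the rest of the text, though: 1848 / 65 is about 28 schools, while the registered title names 20. With 20 schools, 1386 / 20 is about 69 analysed pupils per school, which is closer to 65 as the analysed size. Taken literally, 20 schools lower the power to about 75.5%.

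**The planned model adjusts for baseline; the calculation does not.** A baseline to follow-up correlation of 0.25 would offset the loss exactly: 330 / (1 − 0.25²) = 352. The section ED risk quotes retest reliabilities from .24 to .44. If these carried over to the global score at six months, with the design factor unchanged, effective N would be 330 / (1 − 0.24²) = 350 to 330 / (1 − 0.44²) = 409, and power about 80% to 86%. These are assumptions. They show that a shortfall is not established for the model under Statistical analyses. They do not repair a figure derived without that credit.

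It could also be said that the section describes 1478 itself as a number to recruit. That wording does not help, because 1478 is derived from the 352 needed for the test, before any loss is considered.

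A last objection is that the consequence is small. That is fair: the loss on the plan's own chain is about 2.6 points, and the test, the alpha level and the validity of the result are untouched. None of these objections changes the drop-out arithmetic.

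**Conclusion.** The drop-out step is wrong as written. At the stated 25%, 1848 recruits leave 1386, which is 92 fewer than the minimum the same section sets. The total matches 20% drop-out; 25% corresponds to about 1971 (1972 from the unrounded figure). This follows from the stated numbers alone, and nothing elsewhere in the article corrects it.

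The effect on power is modest and conditional. It is about 77.5% to 78% in place of 80% if the design factor of 4.2 holds, 65 is the analysed cluster size and no credit is taken for the baseline covariate. Other readings of the cluster size move it in either direction (about 75.5% to 86%), and the covariate could offset the loss. The error justifies correcting the figure, but not concluding that the trial is underpowered.

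A reader might also infer that the abstract is wrong. It gives 1848 with neither a drop-out rate nor a power, so it does not carry the error while 1848 is kept.

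**What to change.** Amend the section Sample size/power calculation in one of two ways:

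- state that 1848 allows for 20% drop-out; or
- keep 25%, and state that 1386 are then expected in the analysis, that power is about 77% to 78% with a design factor of 4.2, 65 analysed per school and no baseline adjustment, and that the recruitment figure matching 25% would be about 1971.

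In either case, say whether 65 is the recruited or the analysed cluster size, since the power statement depends on it.

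The cost is a few words and, under the second option, a slightly less favourable stated power. Recruitment has closed, so no further recruitment is asked for. The abstract needs no change while 1848 is kept.
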